## Abstract

**Introduction:**

Cyclin-dependent kinase-like 5 deficiency disorder (CDD) is a neurodevelopmental condition characterized by infantile-onset epilepsy, developmental delay, intellectual and motor disabilities, sleep disturbances, and cortical visual impairment. Currently, there is no treatment for CDD, and epilepsy is a prominent and severe feature of the disorder. Standard anti-seizure medications have limited efficacy in seizure control, leading to detrimental effects on cognitive and motor development in CDD. The gut-brain axis has gained attention in epilepsy research, prompted by evidence of gastrointestinal (GI) symptoms in people with epilepsy. Notably, CDD patients experience GI problems and exhibit alterations in their gut microbiota compared to healthy individuals. We propose targeting the gut-microbiota-brain axis in CDD patients to alleviate seizures and potentially ameliorate other symptoms.

**Methods and analysis:**

The protocol involves a two-step treatment strategy: a 12-week supplementation with alpha-lactalbumin (ALAC), fructooligosaccharides (FOS), and inulin to reduce inflammation, followed by a 12-week supplementation with ALAC/FOS/Inulin plus Sodium butyrate (NaB), to restore the balance of the gut microbiota. Clinical parameters, including seizure frequency, sleep disturbances, and GI discomfort, will be evaluated. Stool samples will be collected to analyse the gut microbiome. Primary objectives are to determine whether supplementation with ALAC/FOS/inulin alone or in combination with NaB can improve neurological features in CDD and to explore their effects on gut microbiota composition. Our study aims to provide insights into the potential benefits of targeting the gut-brain axis in CDD and offer new therapeutic options to improve seizure control and associated comorbidities.

**Ethics and dissemination:**

The study protocol was approved by the local ethics committee (CET 3, n° 4189_17.04.2024_N_bis). Study results will be disseminated by the investigators through presentations at international scientific conferences and reported in peer-reviewed scientific journals.

**Clinical trial registration:**

ClinicalTrials.gov, Identifier NCT06448663

## Introduction

Cyclin-dependent kinase-like 5 (CDKL5) deficiency disorder (CDD) is a severe neurological condition that primarily affects brain development, leading to significant challenges such as early-onset, treatment-resistant seizures, profound developmental delay, intellectual and motor impairments, sleep issues, and cortical visual dysfunction (1). Most individuals with CDD begin experiencing seizures within the first year of life, with 90% showing symptoms by 3 months of age (2). The disorder is estimated to occur in approximately 1 in 40,000–60,000 live births and predominantly affects females, with a gender ratio of 12:1 (3). CDD is caused by pathogenic variants in the *CDKL5* gene, located on the X chromosome, which encodes a serine/threonine kinase highly expressed in the brain. Given the severe neurological impact of CDD, the *CDKL5* gene plays a crucial role in normal brain development and function, particularly in synaptic plasticity and neuronal communication (4). Individuals with CDD often experience various types of seizures, including epileptic spasms (with or without hypsarrhythmia), tonic seizures, generalized tonic–clonic seizures, and complex seizures with multiple phases (such as the hypermotor-tonic-spasms sequence) (5). Epilepsy in CDD patients is highly refractory, and there are few reports concerning response to standard treatment regimens. Alternate therapies are not yet established. Ketogenic diet and vagus nerve stimulation showed heterogeneous results in observational studies (6).

While seizures are a prominent and early symptom of CDD, other neurological issues such as global hypotonia, sleep disturbances, behavioral challenges, movement disorders, and difficulties with swallowing are also significant (7).

Emerging evidence indicates the crucial role of gut microbiota in neurodevelopment through a complex interplay of immune, neuronal, and systemic endocrine pathways. The microbiota–gut–brain axis (MGBA) has been implicated in neurodevelopmental disorders, including autism spectrum disorder, attention deficit hyperactivity disorder, and Rett Syndrome (8).

Recently, the MGBA has been investigated for its involvement in epilepsy (9), starting from the evidence that people with epilepsy (PWE) often show GI symptoms, and patients with inflammatory bowel disease have a higher susceptibility to epilepsy (10). Several studies have suggested significant changes in the fecal microbial composition in animal models of seizures and between PWE and healthy subjects (11–15). Notably, CDD patients experience GI issues, and recent data suggest that gut microbial composition differs from healthy relatives, showing a more pro-inflammatory profile (16). Alterations in the gut microbiota composition might affect microbial metabolites production and release, which in turn can modulate gut homeostasis, local and systemic inflammation (17).

CDD symptoms severely affect patients’ quality of life, and no approved treatments currently exist. Disease management primarily focuses on symptom relief, particularly seizure control, through medications, alternative therapies, and supportive care (18).

The modulation of gut microbiota could potentially alleviate some neurological symptoms by reducing inflammation and improving gut-brain communication (19, 20).

To investigate this strategy, we designed a 32-week interventional study to evaluate possible beneficial effects of special purpose foods in improving CDD clinical phenotype. The protocol’s dietary supplements contain alpha-lactalbumin (ALAC), inulin, fructooligosaccharides (FOS), with/without sodium butyrate (NaB). ALAC is a whey protein that is abundant in human milk, rich in essential amino acids, particularly tryptophan, which is a precursor for serotonin, a neurotransmitter that plays a crucial role in mood regulation, cognitive function and central nervous system homeostasis (21). The balance between pro-inflammatory and anti-inflammatory metabolites generated from tryptophan metabolism is crucial; while some metabolites like kynurenic acid are neuroprotective, others, such as quinolinic acid, can be neurotoxic (22). FOS and inulin are well-known prebiotics that promote the growth and metabolic activity of beneficial intestinal bacterial genera, particularly *Bifidobacterium* and *Lactobacillus*, enhancing SCFA production and supporting gut health (23, 24).

Butyrate, on the contrary, a postbiotic, can exert anti-inflammatory effects, ameliorate oxidative stress-induced damage on intestinal cells, promoting a healthier microbial profile that can lead to improved gastrointestinal function (25, 26).

## Methods and analysis

### Trial objectives

The main objective of the current protocol is to investigate whether ALAC/FOS/Inulin supplementation itself or plus NaB can represent a valid option to reduce seizure frequency in CDD patients.

Moreover, since associated comorbidities have a remarkable impact on patients and families, the goal of improving these symptoms represents a worthy endeavor while awaiting a more definitive cure.

### Trial design

This is a 32-week single-arm, open-label clinical trial of ALAC/FOS/Inulin (MF1, Kolfarma s.r.l. - Italy) vs. ALAC/FOS/Inulin/NaB (MF2, Kolfarma s.r.l. - Italy) aimed at restoring gut homeostasis and gut community health (Figure 1). The intervention will be conducted in a single investigational study centre in Italy, namely the Child and Adolescent Childhood Neurology and Psychiatry Unit at ASST Grande Ospedale Metropolitano Niguarda in Milan, Italy.

**Figure 1 fig1:**
[figure not shown]
Trial design. We planned a 32-week longitudinal intervention based on two sequential interventions. A 12-weeks supplementation has been selected to ensure a sufficient duration for evaluating meaningful clinical changes (according to the primary and secondary outcomes). Wash out periods have been designed to verify the duration of clinical and gut microbiota changes after supplement discontinuation. DBS, dried-blood spot; ALAC, alpha-lactalbumin; FOS, Fructooligosaccharides; MF, Medical Food; NaB, Sodium butyrate.

We planned an interventional study as follows: a 12-week supplementation period with MF1, 4-week washout, 12-week supplementation with MF2, and a final 4-week washout. Patients will undergo full clinical assessments at baseline (enrollment, before starting the first supplementation), after the first supplementation and at the end-of-treatment visit, 1 week after the last supplementation. Stool and dried-blood spot (DBS) samples, food diary, and GI scales will be collected at scheduled time points, as described in the Study Procedures’ paragraph. Gut microbiome characterization, SCFAs (short-chain fatty acids) quantification, clinical scales and dietary intake will be assessed.

### Study treatment

The study involves the use of two medical foods (MF1 and MF2 - Kolfarma s.r.l.) containing ALAC, inulin, FOS, with the addition of NaB in a CDD patient population. Both products are indicated for pediatric age (> 3 years). The product must be taken orally and not parenterally.

MF1 is a dietary supplement aimed at improving intestinal dysbiosis containing ALAC (contains milk derivatives), FOS, inulin, sweetener (steviol glycosides from stevia), emulsifier (polysorbate 80).

The first-round supplementation will be administered for 12 weeks. One dose/day (2 g sachet) is intended to be administered orally once a day after dissolving in water.

MF2 is a special medical purpose food intended for the dietary treatment of drug-resistant epilepsy. It contains ALAC (contains milk derivatives), inulin, FOS, flavors, sucralose, polysorbate 80, and NaB.

The second-round supplementation will be administered for 12 weeks. For participants weighing <30 kg, a 4 g dose (i.e., one 4 g sachet) is intended to be administered orally once a day after dissolving in water, 15 min before meal. For participants weighing ≥30 kg, a 4 g dose (i.e., 4 g sachets) is intended to be administered orally twice a day (12 h interval) after dissolving in water, 15 min before meals.

Intake is not recommended in cases of proven hypersensitivity to one or more ingredients.

No known side effects are reported for the two products used in this study.

If a treatment tolerance problem should develop at any time during the study, the investigator may reduce the patient’s dose, with administration on alternate days. Patients unable to tolerate the treatment even after a dose interruption should be suspended from the study.

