### Participants

The study will enrol 20 CDD patients. The sample size for this study is dictated by the rarity of the condition, 1:40,000 live births (3), and considering that the number of CDD patients in Italy is about 60 (according to the report of the Patients Association “CDKL5 Insieme verso la cura”). The sample size is calculated based on the following assumptions: (1) the clinical success for an enrolled patient is defined as a reduction of at least 50% of the seizure frequency compared to baseline; (2) a clinically significant result is achieved if at least 35% of the enrolled patients reduce the seizure frequency by at least 50%.

With these premises, a McNemar exact test (“after vs. before”), applied to a sample of 20 subjects, reaches a power of 80%, less than an alpha-error of 5%, in verifying clinical success in 35% of cases, using the following inputs: percentage of positives that become negative = 0; percentage of negatives that become positive = 35.

Eligible patients from Italy who meet the defined inclusion and exclusion criteria will be recruited, after signing the informed consent.

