### Study procedures

The schedule of activities planned during the study is summarized in Table 1.

**Table 1 tab1:** Summary of measures and instruments used in the present study.

Study period					
Enrolment		Intervention period			
Timepoint	T0	T1	T2	T3	T4
Enrolment:					
Eligibility screen	X				
Informed consent	X				
Demographics	X				
Medical history	X				
Concomitant medication	X				
Intervention:					
ALAC, FOS, and inulin supplementation		X			
ALAC, FOS, inulin and NaB supplementation				X	
Assessments					
Dietary survey	X	X	X	X	X
Gastrointestinal Severity Index (GISI) (16) scale	X		X		X
Bristol Stool Form Scale (BSFS) (16)	X	X	X	X	X
Clinical global impression– improvement scale (CGI-I) (16)	X		X		X
Motor-Behavioral Assessment Scale (MBAS) (16)	X		X		X
CDKL5 severity assessment (CDD-SA) (29)	X		X		X
Sleep Disturbance Scale for Children (SDSC) (16)	X		X		X
Daily Seizure diary	X	X	X	X	X
Parenting Stress Index questionnaire (PSI-SF) (16)	X				x
Feces collection	X	X	X	X	X
Dried blood spots collection	X	X		X	
Adverse effects	X	X	X	X	X

T0, screening/baseline; T1, first supplementation (MF1); T2, wash-out period; T3, second supplementation (MF2); T4: wash-out period.

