### Subject withdrawal

Patient parents/legal guardians may decide to terminate the study at any time.

The principal investigator, guarantor of the study, may decide to terminate a patient’s participation at any time if the enrolled subject presents adverse events or is not compliant with the study procedures, or after withdrawal of participation consent.

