### Statistical analyses

We will examine longitudinal changes, with particular emphasis on differences between baseline (T0) and post-MF1 (T1), as well as between the second baseline following washout (T2) and post-MF2 (T3).

In descriptive analyses, data will be presented as mean ±SD for continuous variables and as percentages for categorical variables. The primary endpoint will be measured using the McNemar exact test. Differences in continuous variables (scale scores, biomarkers) will be tested using the unpaired and paired t-test for independent and dependent samples, respectively, in case of normally distributed data. For non-normally distributed data, the Wilcoxon rank-sum test will be used for independent samples, and the Wilcoxon signed-rank test for dependent samples. For comparisons among multiple time points, the ANOVA (or Kruskal-Wallis test for non-parametric data) will be applied to independent samples, while repeated measures ANOVA (or Friedman test for non-parametric data) will be used for dependent samples. When appropriate, a *post hoc* test (e.g., Bonferroni correction or Tukey’s HSD) will be performed to adjust the *p*-value.

A p-value < 0.05 will be considered statistically significant.

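### Patients who cannot tolerate the product are told to leave the study, so an MF1 stopper has no scheduled post-baseline value on the clinical scales (minor, cheap to correct)

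*Protocol article*

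**What the plan says.** The Study treatment section sets out a sequence for poor tolerance. The investigator may first reduce dosing to alternate days, and a dose interruption is also mentioned. If these fail, the instruction is: "Patients unable to tolerate the treatment even after a dose interruption should be suspended from the study". The thing left is the study, not the product.

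The Subject withdrawal section adds a discretionary power: the principal investigator may end "participation at any time if the enrolled subject presents adverse events", among other reasons.

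Table 1 defines its columns as "T0, screening/baseline; T1, first supplementation (MF1); T2, wash-out period; T3, second supplementation (MF2); T4: wash-out period". GISI, CGI-I, MBAS, CDD-SA and SDSC are marked at T0, T2 and T4, and PSI-SF at T0 and T4. The seizure diary, stool samples and adverse effects are marked at every time point. There is no column for early termination.

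The Trial design section places full clinical assessments at baseline, "after the first supplementation and at the end-of-treatment visit, 1 week after the last supplementation". The Figure 1 legend gives the purpose of the off-product phases: "Wash out periods have been designed to verify the duration of clinical and gut microbiota changes after supplement discontinuation".

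**The concern.** Because the rule ends participation and not just intake, the patient's remaining scheduled assessments go with it. For the scales this matters more than for the diary: they have no time point during MF1, so the first post-baseline value is due only at T2. The patients lost are selected by poor tolerance. Any mean or median change on SDSC, GISI or the other scales would be computed on those who could take the product. A gut-directed product could plausibly cause gastrointestinal intolerance, which GISI would register, but the document does not say what tolerance problems to expect.

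The rule also sits awkwardly with the design. Observation after discontinuation is one of the stated purposes of the washouts, yet it is given up for those who discontinue early.

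**Working it through.** The plan gives no figure on this point, so there is none to reproduce. The check sets the rule against the schedule and counts.

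**Inputs.** 20 patients enrolled (Participants); 12 weeks of product and 4 weeks of washout in each period (Trial design); scale time points (Table 1); exit on persistent intolerance (Study treatment).

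**Scheduled scale values lost if the rule is followed as written**

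| Stop during | Time point lost | Scales due there | Lost | Scale values remaining |
|---|---|---|---|---|
| MF1 | T2 | GISI, CGI-I, MBAS, CDD-SA, SDSC | 5 of 5 | T0 only |
| MF2 | T4 | the same five plus PSI-SF | 6 of 6 | T0 and T2 (PSI-SF: T0 only) |

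An MF1 stopper also misses T4. If that patient never receives MF2, a T4 value would say nothing about MF2, so it is not counted as a loss.

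Not all of these scales carry equal weight. The Efficacy endpoints section names SDSC and GISI as secondary outcomes, and a global impression scale and PSI-SF as other outcomes. MBAS and CDD-SA appear only in Table 1, with no efficacy threshold.

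**Weight of one stop.** 1 / 20 = 5% of the T0-T2 pairs. This is the weight of one patient, not an estimate of bias.

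**Time from the stop to the end of the period.** For a stop at the end of week w: (12 - w) + 4 = 16 - w weeks.

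- w = 1: 15 weeks
- w = 6: 10 weeks
- w = 11: 5 weeks
- limits: 16 weeks (w = 0) and 4 weeks (w = 12)

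This bears on the remedy too. After a stop in week 1, a T2 value taken at the end of the washout would be about 15 weeks off product and would say little about MF1. An assessment at the time of the stop is more useful.

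**Which analyses are exposed**

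- *Seizure responders:* not affected. The success criterion is set on enrolled patients: "a clinically significant result is achieved if at least 35% of the enrolled patients reduce the seizure frequency by at least 50" per cent. A stopper stays in the denominator.
- *SDSC and GISI thresholds* (decrease of at least 5%; decrease of at least 2 points): not affected if a stopper with a missing value counts as not achieving the threshold.
- *Continuous scale changes* (the paired tests in Statistical analyses): exposed, because a pair needs a post-baseline value.
- *Stool contrast for MF1:* depends on when T1 falls. Table 1 labels T1 as the MF1 period, so a sample may precede the stop. Statistical analyses instead describes "differences between baseline (T0) and post-MF1 (T1"; if T1 is taken after MF1 ends, an early stopper has no T1 sample.

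**The case against.** The strongest reply is that the text forces less than it seems to, and that the lost data are worth little.

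- *Adverse effects.* A reader might infer that adverse effects are not followed once the product is stopped. The article does not say so. It is a condensed account, and safety follow-up after exit is commonly left to the full protocol. That inference is not supported.
- *Subject withdrawal.* A reader might take this section as a second rule forcing exit. It says only that the investigator may end participation, so the patient can also be kept in follow-up. Only the Study treatment sentence directs exit.
- *Meaning of the rule.* Suspension could mean a pause. But the sentence applies after an interruption has already failed, and no return rule is given, so exit is the natural reading.
- *Visit wording.* The Trial design visits are tied to the end of supplementation and not to week numbers, so they could be read as covering an early stopper. This is possible, particularly for the visit 1 week after the last supplementation. But nothing links either visit to an early stop, and the tolerance rule would already have removed the patient.
- *Value of the data.* This is a single-arm before-after study, so there is no randomised comparison to protect, and scale values long after a stop say little about the product. This stands, and it shapes the fix.
- *Size.* The Study treatment section states: "No known side effects are reported for the two products used in this study". Alternate-day dosing comes before exit. Few removals are likely.

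What remains is a stated rule that removes scheduled scale values selectively, where a different verb would keep them.

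**Conclusion.** The point holds as a minor one. As written, the tolerance rule merges stopping the product with leaving the study. An MF1 stopper then has no scheduled post-baseline value on five scales, two of them secondary outcomes. An MF2 stopper loses the T4 values unless the post-supplementation visit is taken to apply. The effect falls on the continuous scale changes, which would describe tolerators only.

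A reader might go further and infer that the responder result is biased. The enrolled denominator does not support that. The size of any bias in the scale changes cannot be derived because no removal rate is given; with no known side effects and a dose-reduction step first, it is probably small.

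The conclusion assumes that suspension means exit and that Table 1 is the full schedule of the scales.

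**What to change.** In Study treatment, replace the study-exit instruction with *should stop the product*. Then add, for as long as consent stands:

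1. Do the full clinical assessment at the time of the stop, and label it as an at-stop value.
2. Continue the seizure diary and adverse-effect recording through the assessments already scheduled for that period: T1/T2 for MF1, T3/T4 for MF2.
3. Where SDSC or GISI values are missing, count early stoppers as not achieving the threshold.
4. Patients who could not tolerate MF1 need not receive MF2. Report MF2 results as applying to patients who tolerated MF1.

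The Subject withdrawal section can stay as it is, since it already leaves the decision to the investigator, and families remain free to withdraw.

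The cost is a short wording amendment and, for the few families concerned, one assessment at the stop, less than 16 weeks of further diary, and the remaining scheduled contacts of that period. The sample size and product exposure do not change.

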### Prohibited therapies

To reduce the effect of spurious variables on study endpoints, therapeutic stability is expected from at least 4 weeks prior to enrolment. The use of antibiotics is not recommended during the study, as it may alter the gut microbiota. However, if deemed necessary, a doctor may prescribe them, provided that the research team is informed. There are no contraindications to taking other drugs during the study.

Any change in treatment will be recorded in the medical record.

### Participants

The study will enrol 20 CDD patients. The sample size for this study is dictated by the rarity of the condition, 1:40,000 live births (3), and considering that the number of CDD patients in Italy is about 60 (according to the report of the Patients Association “CDKL5 Insieme verso la cura”). The sample size is calculated based on the following assumptions: (1) the clinical success for an enrolled patient is defined as a reduction of at least 50% of the seizure frequency compared to baseline; (2) a clinically significant result is achieved if at least 35% of the enrolled patients reduce the seizure frequency by at least 50%.

With these premises, a McNemar exact test (“after vs. before”), applied to a sample of 20 subjects, reaches a power of 80%, less than an alpha-error of 5%, in verifying clinical success in 35% of cases, using the following inputs: percentage of positives that become negative = 0; percentage of negatives that become positive = 35.

Eligible patients from Italy who meet the defined inclusion and exclusion criteria will be recruited, after signing the informed consent.

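### The stated 80% power does not belong to the exact McNemar test named: with the plan's inputs that test has 75.5% power two-sided or 88.2% one-sided, and the sidedness is not given

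*Protocol article*

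**What the plan says.** The protocol article, Participants, fixes the size: "The study will enrol 20 CDD patients". It gives two grounds. One is how few patients with this disorder there are in Italy. The other is a power statement for a McNemar exact test, "applied to a sample of 20 subjects, reaches a power of 80%, less than an alpha-error of 5" per cent. The inputs are listed: "percentage of positives that become negative = 0; percentage of negatives that become positive = 35" (per cent).

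The same section defines success for a patient as at least a halving of seizure frequency. For the trial it says that "a clinically significant result is achieved if at least 35% of the enrolled patients reduce the seizure frequency by at least 50" per cent.

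The Statistical analyses section names the same test: "The primary endpoint will be measured using the McNemar exact test". It adds that "A p-value < 0.05 will be considered statistically significant". Neither section says whether the test is one-sided or two-sided.

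**The concern.** An exact McNemar test on 20 pairs is discrete. Its rejection limit is a whole number of responders, so its power can take only certain values. When every switch is in one direction, the limit and the power follow at once from the binomial distribution, and a stated figure of 80% can be checked directly. It does not come out under either sidedness.

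This statement is the only quantitative support for 20 patients. The article gives the test, the inputs and the result explicitly, so this is a stated figure that does not fit the stated test, not a detail left to another document. A reader would take from it a 20% chance of missing a true 35% response. For the two-sided test that chance is nearly 25%.

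**Working it through.** **Inputs.** From Participants: n = 20; rate of switching from non-responder to responder 0.35; reverse rate 0; alpha 5%; target power 80%. From Statistical analyses: exact McNemar test, p < 0.05. Assumed: all 20 patients evaluable. Sidedness is not given, so both versions are shown.

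**1. Reproducing the 80%.** The large-sample McNemar formula, with total discordance pd = 0.35 and difference d = 0.35, is

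n = [z(0.975)·√pd + z(0.80)·√(pd − d²)]² / d²

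- √0.35 = 0.5916 and √(0.35 − 0.1225) = 0.4770
- n = [1.960 × 0.5916 + 0.8416 × 0.4770]² / 0.1225 = 19.89, rounded up to 20
- power at n = 20: Φ[(0.35·√20 − 1.960 × 0.5916) / 0.4770] = 80.25%

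Both the 20 and the 80% are recovered. The one-sided version of this formula gives n = 15.4, and 89.3% power at n = 20, so it does not recover them.

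**2. The exact test.** With no reverse switches, the number of responders X is Bin(20, 0.35). The exact p-value is 0.5^X one-sided and 2 × 0.5^X two-sided.

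| X | one-sided p | two-sided p | P(at least X responders, true rate 35%) |
|---|---|---|---|
| 4 | 0.0625 | 0.125 | 95.6% |
| 5 | 0.031 | 0.0625 | 88.2% |
| 6 | 0.016 | 0.031 | 75.5% |
| 7 | 0.008 | 0.016 | 58.3% |

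- Two-sided: the first p below 0.05 is at X = 6, so power is 75.5%.
- One-sided: the first p below 0.05 is at X = 5, so power is 88.2%.

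The attainable values step from 88.2% to 75.5%; 80% is not among them.

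**3. Distance from 80%.** Two-sided exact power is 79.9% with 21 patients and 83.7% with 22. At n = 20 it would be 80% if the true rate were 36.6%. One-sided, 18 patients would already give 81.1%.

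**4. The clinical bar (a separate quantity).** 35% of 20 is 7. From the table, P(X ≥ 7) = 58.3% when the true rate is 35%; a true rate of about 41.8% would be needed for an 80% chance. A result of exactly 6 of 20 (30%) is significant two-sided but below the bar. Its probability at a true rate of 35% is 75.5% − 58.3% = 17.1% (from unrounded values, 0.7546 − 0.5834 = 0.1712).

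**The case against.** The best defence is that sidedness is open. If the test is one-sided, 88.2% exceeds 80%, and the claim that the test reaches 80% is true as a lower bound. This stands as far as it goes: it cannot be said flatly that the trial has only 75.5% power. But the figure would still not be the power of the named test, and 18 patients would then have been enough for 80%. The close match with the two-sided approximation suggests a two-sided intention. That is inference, since the article does not name its formula.

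The gap is also small, and the article says that the number of patients is governed by the rarity of the disorder. Both points stand, and they limit how serious the correction is.

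Three stronger readings are tempting, and the document supports none of them.

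- A reader might infer that the 58.3% shows the 80% to be badly wrong. The article attaches its 80% to the McNemar test, and the chance of seeing at least 7 of 20 concerns a different event. Any bar placed at the assumed true rate is met only somewhat more than half the time.
- A reader might infer that the 35% bar and the p < 0.05 rule contradict each other. Clinical and statistical significance can legitimately differ, and the Statistical analyses section contains no 35% rule. What is open is only which of the two decides success.
- A reader might infer that withdrawals lower the power further. The article gives no withdrawal rate, and handling of withdrawals is commonly left to a fuller document, so no figure for this can be charged to the plan.

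**Conclusion.** The power statement is wrong as written. It names an exact test and gives a power that no exact version of that test has with the listed inputs. The correct figure is 75.5% two-sided, about 4.5 points below the claim, or 88.2% one-sided, about 8 points above it. These values assume 20 evaluable patients, a true responder rate of 35%, no reverse switching and a 5% level. They concern the threshold of at least a 50% reduction, which is the one used in the sample size paragraph.

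The correction is minor to moderate. The number enrolled, the test and the analysis can stay as they are. The unclear role of the 35% bar is an additional remark and not part of the arithmetic error.

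**What to change.** In Participants, state the sidedness and replace the power sentence. If the test is two-sided, a suitable text is:

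> With 20 evaluable patients and a true responder rate of 35%, the two-sided exact McNemar test at the 5% level (6 or more responders) has about 75% power.

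If it is one-sided, the limit is 5 or more responders and the power is 88%. Since Efficacy endpoints counts responders in both rounds of supplementation and at three thresholds, the sentence should also say which round it refers to and that it concerns the 50% threshold. The sidedness should be repeated in Statistical analyses.

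Add one sentence saying whether success is decided by p < 0.05 or by at least 7 of the 20 enrolled patients responding. If it is the latter, report the 58% probability as its own figure, apart from the power of the test.

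The cost is one reworded paragraph and, if the test is two-sided, a slightly less favourable number. No further patients are needed.
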